##### Assessments

Table S1 in Multimedia Appendix 1 gives an overview of all assessments in WP 4.

##### Feasibility Parameters

###### Recruitment

The number of contacted and recruited survivors with reasons for nonrecruitment will be recorded by the study nurses at each site.

###### PA Parameters

PA will be measured by an accelerometer as described for WP 1 at baseline and after 6 months. In addition, the PA will be tracked continuously with the Polar watch (Polar Global). At each follow-up discussion with the central coaches, the survivors will be asked about their participation in the agreed PA program and, if applicable, reasons for nonparticipation.

###### Compliance (Adherence and Retention)

Compliance with the PA intervention will be assessed based on the PA measurements described above. In addition, we will record the number of contacts of each survivor with the central and local coaches and the number of missing information at each study time point. Dropouts and reasons for dropout will be assessed by the study nurses.

###### Safety

Safety and adverse events will be assessed by the central coaches during follow-up calls.

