##### Overview

WP 4 aims to develop and feasibility test a sustainable and safe PA intervention for survivors of childhood cancer based on the results obtained in WPs 1 to 3. Norway, Finland, and Germany will participate in WP 4. The study will comprise two study visits (baseline and after 6 months), including self-reported questionnaires, interviews, measurement of PA, and PF tests (Table 1; Table S1 in Multimedia Appendix 1). In between, the survivors will participate in a personalized PA intervention, followed by central and local coaches.

In specific, we aim to do the following:

Describe the adherence to and acceptability, satisfaction, and safety of the personalized PA interventionTest the involvement of local structures (parents, school, teachers, peers, community and school nurses, and sports clubs) to improve the PA of survivorsAssess the effect of the intervention on PA, attitude toward PA, QoL, fatigue, and PFExplore the experiences of survivors of childhood cancer and their parents of participating in the PA interventionExplore the central coaches’ experiences providing the intervention and collaborating with local structures

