##### Intervention

The exercise intervention will last 6 months and starts with a personal motivational interview (MI) session at the baseline study visit. For each survivor, a central study coach is appointed who performs the MI and, together with the participant, defines a personal target of duration and intensity of PAs per week. The MI technique is a communication method that involves enhancing a patient’s internal motivation to change [75]. During this session, local structures (local coaches) will be identified that can help and support the survivor to reach their PA goals and maintain a more active lifestyle after the intervention. On the basis of this assessment, individualized PAs are defined and implemented into a survivor’s daily life. Each survivor will get a written personalized plan at the end of the session and a Polar watch (Polar Global) to track their behavior and provide immediate feedback on their achievements.

The central study coach will follow up with the survivor and local coaches with a phone call based on a predefined schedule of decreasing frequency over time (Table S1 in Multimedia Appendix 1). During the follow-up phone calls, the coach uses MI-inspired techniques and a standardized guideline to discuss adherence, motivation, progress, and possible problems. The training program can be adapted, and solutions for solving problems will be searched. The central coach will also follow the PA behavior in real time based on the Polar watch and set up an additional follow-up contact if the survivor struggles to reach his or her activity goals. The central coaches will be trained in the use of MI techniques to be used in the initial and follow-up conversations with survivors.

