##### Data Management

All self-reported questionnaires will be answered electronically either on the study tablet PCs during the study visits (baseline and 6 months) or from home via a personal link (2 months). The questionnaires will be linked to the TSD secure data server at the University of Oslo, where the data will be stored. Device-measured data (Actigraph and Polar watch [Polar Global]) will be downloaded and added to the folder on the TSD. Information assessed by the study nurses, central coaches, and assessors of the physical testing will be collected in Microsoft Excel files and stored on TSD. All information will then be merged into a master data file using the statistical software STATA (version 17 or newer; StataCorp LLC).

##### Data Analyses WP 4

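### WP 4 names one route for adverse events, the coach who delivers the intervention, on calls that become less frequent, so the aim of describing safety is at risk of under-ascertainment

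*Protocol article*

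**What the plan says.** The WP 4 Overview lists safety among the features of the intervention to be described. The Safety paragraph under Feasibility Parameters is a single sentence: "Safety and adverse events will be assessed by the central coaches during follow-up calls". It fixes both the assessor and the occasion.

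The Intervention section describes that assessor: "a central study coach is appointed who performs the MI and, together with the participant, defines a personal target of duration and intensity" of activity. The coach then follows up "with a phone call based on a predefined schedule of decreasing frequency over time". Calls use "a standardized guideline to discuss adherence, motivation, progress, and possible problems", and the programme can be adapted during them. The coach also watches the activity-tracker data and will "set up an additional follow-up contact if the survivor struggles to reach his or her activity goals".

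Other contacts are described, but none is tied to adverse events in the text:

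- The Overview states: "The study will comprise two study visits (baseline and after 6 months), including self-reported questionnaires, interviews, measurement of PA, and PF tests".
- Under Data Management, questionnaires are answered on tablets at the two visits "or from home via a personal link (2 months"). The section on attitudes toward activity gives the content of the 2-month assessment.
- Under Compliance, "Dropouts and reasons for dropout will be assessed by the study nurses". The number of contacts with central and local coaches is recorded for each survivor.
- Under PA Parameters, the coaches ask at each follow-up discussion about participation and, where relevant, reasons for not taking part.

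The article refers to Table S1 in Multimedia Appendix 1 for the full list of WP 4 assessments and for the call schedule. That table is not available here.

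**The concern.** The person who sets the activity targets, encourages adherence and adapts the programme is also the only person named as recording its harms. The occasions for recording become sparser over the 6 months. The chance that an event is recorded may therefore depend on the month in which it occurs, on whether the child answers the phone, and on how the person delivering the programme asks about and interprets a problem.

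WP 4 has a single open arm, so no comparison group would show up incomplete capture. What is at stake is the credibility of one descriptive result, the safety profile, which is meant to help prepare a later randomized trial. A low event count that could reflect few events or few opportunities to report them would be hard to interpret.

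**Working it through.** The plan states no event rate, capture rate, safety sample size or safety threshold, so it has no figure to reproduce. The check has two parts: a comparison of the described contacts, and an illustration of what a low count could mean.

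**1. Which contacts could bring an event to light**

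| Contact | Who | Stated purpose | Adverse events named? |
|---|---|---|---|
| Follow-up calls, decreasing frequency | Central coach | Adherence, motivation, progress, problems | Yes, in the Safety paragraph |
| Extra contact prompted by the watch | Central coach | Difficulty reaching goals | No |
| Question on nonparticipation | Central coach | Reasons for not taking part | No |
| 2-month questionnaire from home | Survivor | Attitudes toward activity | No |
| 6-month visit | Site staff, survivor | Questionnaires, interviews, activity, fitness tests | No |
| Dropout record | Study nurse | Dropout and its reason | No |

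The first three rows depend on the coach. Of the last three, the dropout record applies only to children classed as dropouts. A child who remains enrolled but misses calls has the 2-month questionnaire and the 6-month visit, and the article gives neither a safety question.

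**2. What zero recorded events would mean**

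Inputs: n = 30 (planned, approximate, from Study Design, Study Population, and Inclusion Criteria) and n = 23 (included by January 2022, from Results). The capture probability s is an **assumption**, because the documents give none.

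One-sided 95% upper bound on the share of children with an event, given zero recorded: U = (1 − 0.05^(1/n)) / s.

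- n = 30, s = 1: 1 − 0.05^(1/30) = 9.5%
- n = 23, s = 1: 1 − 0.05^(1/23) = 12.2%

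| Assumed s | n = 30 | n = 23 |
|---|---|---|
| 1.00 | 9.5% | 12.2% |
| 0.90 | 10.6% | 13.6% |
| 0.75 | 12.7% | 16.3% |
| 0.50 | 19.0% | 24.4% |

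Chance of recording at least one event if 10% of children truly have one (also an assumption), from 1 − (1 − 0.10·s)^n with n = 30: 95.8% at s = 1, 90.4% at s = 0.75, 78.5% at s = 0.50.

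The s = 1 row reflects sample size alone and says nothing about the capture method. Only the change down each column relates to this point, and it follows entirely from the assumed s.

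**The case against.** The article is a condensed account, and the full schedule sits in Table S1. Adverse-event items at 2 or 6 months may be listed there. That stands: the statement that there is one route applies to the article's text only.

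A reader might infer that events are in fact missed. The documents do not support this. The calls are scheduled, active contacts with a standardized guide that covers problems, and a coach can ask about the whole interval since the last call. Wider spacing lengthens recall; it does not leave time unobserved. Only a risk can be claimed.

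A reader might also infer that an injured or disengaged child has no way to be heard. That goes too far. Nurses, not coaches, record dropout reasons. An injury that reduces activity would tend to show on the watch and prompt a contact, and coaches ask why a child is not participating. These safeguards reduce the risk where it might seem greatest. What remains is that none of them asks about adverse events as such, and two of the three still run through the coach.

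Finally, one might infer that a decision to proceed to a randomized trial would be biased. The article sets no rule by which WP 4 would declare the intervention safe enough. The aim is to describe, and the analysis is mainly descriptive. The consequence is a weaker description, not a wrong decision under a stated criterion.

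**Conclusion.** The point holds in a limited form. In the article, the only named route for WP 4 adverse events is the central coach, who also delivers the intervention, on calls that thin out over time. Safety is a stated aim, and this is a method the plan has chosen, not merely a detail left out. The risk of under-ascertainment falls mainly on minor events, late in follow-up, and among children who stay enrolled but miss calls.

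Its size cannot be derived from the documents. The bounds of 9.5% and 12.2% for zero events hold even if every event is captured; the higher figures are illustrations under assumed capture rates. The conclusion assumes that Table S1 adds no other adverse-event inquiry; if it does, the point is largely met. For a descriptive pilot of about 30 children this is a worthwhile, inexpensive improvement and not a threat to the study's main purpose.

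**What to change.** First check Table S1. Unless it already provides this:

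1. Add one structured item (what happened, when, related to activity or not), answered by the child or a parent, to the existing 2-month electronic questionnaire and to the 6-month visit.
2. Have the study nurse ask the same item when recording a dropout and its reason.
3. Report events by source (coach call, self-report, nurse), with person-time and the contact counts that the plan already records. A reader can then see whether events follow the number of contacts.

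The cost is one item on existing instruments and a minor amendment, with no new staff or visits. The downside is timing. By January 2022, 11 of the 23 included had completed, so at most 23 − 11 = 12 of them, plus up to 30 − 23 = 7 later recruits, could be asked prospectively, and some of the 12 may already have passed the 2-month contact or left the study. Children who have finished can be asked only in retrospect, with recall error, and their answers should be labelled as such in the report.

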###### Subjective Rating of the Intervention and Its Motivational Features

At the end of the intervention, the survivors will give their subjective rating of satisfaction with participation in and intended sustainability of the PA intervention. The questions will be developed specifically for this study.

###### Attitude Toward PA (Barriers, Perceived Physical Competence, Perceived Enjoyment, and Motivation)

Attitudes toward PA will be assessed at baseline and at 2 and 6 months. The same questions as in WP 1 will be used to assess *barriers to PA*. *Perceived physical competence* (3 items) and *perceived enjoyment* (5 items) will be measured by items from the *Children’s Attraction to PA* scale [76-78]. *Motivation toward PA* will be measured using the Behavioral Regulation in Exercise Questionnaire 2 [79].

###### QoL and Fatigue

At baseline and 6 months, survivors will fill in the same questionnaires as in WP 1 to assess QoL and fatigue (only self-reported version and no parent module).

###### PF Assessment

PF will be assessed during the study visits at baseline and after 6 months. All sites will perform a CPET and 1-minute STS test according to the same protocol as described for WP 2. In addition, Oslo and Bergen will perform the same isometric strength tests (knee extension and chest press) as in WP 2. Turku will perform the same knee extension test as WP2 but on its own device as well as a dynamic upper extremity lifting test (standing with 5 kg dumbbells for women and 10 kg for men; number of repetitions are reported). Essen will perform the same isometric knee extension and chest press as in WP2 but on their own devices.

##### Qualitative Interviews With Survivors, Parents, and Central Coaches

Feasibility, acceptability, sustainability, and satisfaction with the PA intervention will also be assessed by qualitative in-depth interviews in a subsample of survivors and their parents from the Oslo site at the 6-month visit (8-15 survivors and their parents until information saturation is reached). Furthermore, the central coaches will participate in a focus group interview to explore their views on feasibility, acceptability, and satisfaction. The interview guides are provided in Multimedia Appendix 2.

##### Data Management

All self-reported questionnaires will be answered electronically either on the study tablet PCs during the study visits (baseline and 6 months) or from home via a personal link (2 months). The questionnaires will be linked to the TSD secure data server at the University of Oslo, where the data will be stored. Device-measured data (Actigraph and Polar watch [Polar Global]) will be downloaded and added to the folder on the TSD. Information assessed by the study nurses, central coaches, and assessors of the physical testing will be collected in Microsoft Excel files and stored on TSD. All information will then be merged into a master data file using the statistical software STATA (version 17 or newer; StataCorp LLC).

##### Data Analyses WP 4

###### Quantitative Data

As this is a feasibility study, we will mainly use descriptive statistics to present the study results. We will use numbers and proportions to describe categorical variables and means, SDs (or median and IQR if the data are skewed), and ranges to describe continuous variables. *P* values will be calculated based on appropriate univariable and multivariable models depending on the outcome and adjusted for the study site by introducing a random intercept (mixed model). *P* values are interpreted as flagging trends and not as hypothesis tests.

###### Qualitative Data

Qualitative content analyses of interview transcripts will be performed [70].

### Ethics Approval

The PACCS study has been approved by the Norwegian Regional Committee for Medical Research Ethics (WP 1,3,4: 2016/953 and WP 2:2018/739), the Data Protection Officer at Oslo University Hospital, and by the equivalent institutions in Finland, Denmark (file. H-19032270), Germany, and Switzerland (Ethics Committee of Northwestern and Central Switzerland; project ID: 2019-00410). Approvals from the regional ethical committees for medical and health research at all sites and the project owner institution are the assumptions for the implementation of the project. As most of the participants will be too young to provide valid informed consent, they will receive written and verbal information about the studies adapted to their developmental stage. Parents or legal guardians will provide written consent on their behalf. School nurses, physical education teachers, and other relevant parties participating in WP 3 will provide informed consent in writing. This protocol is written according to the SPIRIT (Standard Protocol Items: Recommendations for Interventional Trials) guidelines [80].

## Results

Research activity for this study commenced in November 2016 with the piloting of questionnaires and recruitment to WP 1 at the Oslo, Norway site. The project received funding from the Research Council of Norway for the period from June 2018 to June 2022. International collaboration was established after June 2018. Data collection at all sites was initiated by October 2020 for WP 1 and concluded on January 2021, with 517 survivors of childhood cancer included. Data cleaning and analysis are currently underway. A total of articles are under preparation for publication. Data collection for WP 2 was initiated in January 2019 and concluded in December 2020, with 157 survivors of childhood cancer and 113 controls included. Data cleaning and analysis are currently being conducted. A total of 6 articles are planned based on the WP 2 data set. Data collection for WP 3 was initiated in January 2018. Patient and parent interviews were concluded in July 2020, with 63 survivors of childhood cancer and 68 parents. Interviews with local stakeholders were initiated in January 2020 and concluded in October 2020, with a total of 18 participants interviewed (teachers, special needs teachers, and school nurses). Data from the patient and parent interviews have been analyzed and are currently being written for publication. A total of 2 articles have been published as of January 2022 [81,82], and 2 more are under preparation for publication. Data from interviews with local stakeholders are currently being analyzed, and 1 article is planned. WP 4 recruitment was initiated in May 2021 and is still ongoing as of January 2022. The study is planned to be completed by July 2022. As of January 2022, 23 survivors of childhood cancer have been included, of which 11 have completed the intervention. Detailed plans for data analyses for WPs 1 to 4 are described in the "Assessments, Power Calculations, and Statistical Analyses" section.

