**Questionnaires**												
	Demographic variables (age and gender)^h,i^	✓		✓		✓		✓		✓		
	Self-reported PA^j,k^, including recreational sports participation and active commuting habits^h,i^	✓										
	Physical education^l^	✓										
	Perceived PA barriers: 15 items covering reasons for not being physical active^m^	✓								✓		
	Attitude toward PA (perceived physical competence, perceived enjoyment, and motivation)									✓		
	Television or screen time^n^	✓										
	Diet, including sugar rich beverages^h,o^	✓										
	Sleep^i^	✓										
	Quality of life (PedsQL^p^)	✓								✓		
	Fatigue (PedsQL MDF^q^ scale)	✓								✓		
	Psychological adjustment (SDQ^r^)	✓										

^a^WP: work package.

^b^For WP 1, 2, and 4: ActiGraph model GT3X+, ActiGraph LLC; for WP 4: real-time tracking of PA over 6 months (time spent in activity, type of activity, and intensity and steps) using a Polar watch (Polar Global).

^c^Cardiopulmonary exercise testing on a treadmill.

^d^Cardiopulmonary exercise testing on a bike.

^e^Isometric knee extension strength is tested on the custom-built strength ergometer similar to WP 2 in Bergen and Oslo and on sites' own commercial devices in Turku and Essen.

^f^Upper arm strength is tested as isometric chest press on the custom-built strength ergometer similar to WP 2 in Bergen and Oslo and on sites' own commercial device in Essen. Turku performed a dynamic upper extremity lifting test in a standing position.

^g^DXA: dual-energy x-ray absorptiometry.

^h^Items from the Health in Adolescents study [34].

^i^Items from the Physical Activity in Norwegian Children Study [35].

^j^PA: physical activity.

^k^Number of counts per minute (cpm; primary outcome); fulfillment of physical activity (PA) recommendations (>60 minutes of moderate to vigorous PA per day); PA intensity categories (counts translated into metabolic energy equivalents of intensities): sedentary time (<100 cpm), light (100-1999 cpm), moderate (2000-5999 cpm), and vigorous (≥6000 cpm).

^l^Items from the Relevance of Physical Activity Contexts in the Everyday Life of Adolescents study [36].

^m^Constructed for the purpose of the Physical Activity and Fitness in Childhood Cancer Survivors study based on literature review and expert and user input.

^n^Items from the Health Behavior in School-aged Children study [37].

^o^Items from the UngKost [38].

^p^PedsQL: Pediatric Quality of Life Inventory [39].

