##### Assessment of PA and Sedentary Time by Accelerometer

PA and sedentary time will be assessed objectively by accelerometers worn for 7 days during the awake time to measure accelerations of +6 G to –6 G (ActiGraph model GT3X+, ActiGraph LLC). The sample rate of the accelerometer is set to measure the raw signals at 30 Hz. Total PA will be described as the number of counts per minute (cpm), which is a measure of the volume of PA assessed by the accelerometer. The accelerometer data will be uploaded by all collaborators to a central server located at the Norwegian School of Sport Sciences and analyzed at one site. Accelerometer measurements with at least four valid measurement days (≥480 min/day) will be included in the analysis.

The activity counts from the accelerometers will be translated into metabolic energy equivalents of intensities as sedentary time (<100 cpm), light (100-1999 cpm), moderate (2000-5999 cpm), and vigorous (>6000 cpm) PA [42]. Participants will be categorized as reaching the international recommendations for PA if they engage in at least 60 minutes of moderate to vigorous PA (≥2000 cpm) per day on average over valid accelerometer measurement days.

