##### Reference Material

Age- and sex-stratified reference material for the primary and most of the secondary outcomes are available for comparison of marginal means and will be provided from several large-scale studies among healthy children and adolescents. References on PA and sedentary time will be available from two Norwegian studies—the Physical Activity among Norwegian Children study wave 2 (N=3538; age 9 and 15 years) [35], Health in Adolescents study (N=1528; age 11 and 13 years) [34]—and one German study—the German Health study (N=1500-2000; age 6 to 17 years) [44]. Age- and sex-stratified national reference materials are also available for attitudes toward physical education (REPAC) [36], screen time (Health Behavior in School-aged Children study) [37], and psychosocial measures (PedsQL [45], PedsQL Multidimensional Fatigue Scale [46], and SDQ [47]).

##### Power Calculation and Statistical Analyses WP 1

From studies in the general Norwegian population, we know that children aged 9 to 15 years engage in an average of 549 (SD 180) cpm (measured by accelerometer) [35]. We assumed reduced PA levels in survivors of childhood cancer. To estimate a difference of 10% in objectively measured PA between survivors of childhood cancer and healthy controls (494 vs 549 cpm, SD 180 for both; power=80%; significance level *P*<.05, one-sided), we need to include 250 survivors of childhood cancer. Given the heterogeneity in the expected sample (age and diagnoses) and to facilitate subgroup comparisons, we aim to include at least n=500 in WP 1 to facilitate subgroup comparisons.

Descriptive statistics will be used to present the levels of PA (including different intensity measures and activity patterns) and sedentary time of survivors of childhood cancer compared with the reference materials and PA recommendations. Multilevel models (mixed models) will be used to adjust for the different study sites as random intercepts. We will perform univariable and multivariable multilevel regression models (linear, logistic, or ordinal depending on the outcome) to (1) assess the clinical and sociodemographic factors associated with meeting the PA recommendations in survivors of childhood cancer; (2) assess clinical and sociodemographic factors associated with different patterns or levels of PA and sedentary time; and (3) assess the associations among PA patterns or levels (exposure) and QoL, fatigue, and other health behaviors.

#### WP 2

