###### PA Measures

Whenever the time between participation in WP 1 and recruitment in WP 2 exceeds 3 months, PA will be remeasured by accelerometers as described above (WP 1).

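### The WP 1 and WP 2 physical activity models name no term for when the accelerometer was worn; adding month of wear would cost almost nothing

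*Protocol article*

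**What the plan says.** - **Measurement.** The section on accelerometer assessment states: "PA and sedentary time will be assessed objectively by accelerometers worn for 7 days during the awake time". No repeat within WP 1 is described. A record counts if it has at least four valid days. A footnote to Table 1 gives the primary outcome: "Number of counts per minute (cpm; primary outcome".
- **Timing.** The Results section gives a start date for one site only: "Research activity for this study commenced in November 2016 with the piloting of questionnaires and recruitment to WP 1 at the Oslo, Norway site". It continues: "International collaboration was established after June 2018". It closes WP 1 with: "Data collection at all sites was initiated by October 2020 for WP 1 and concluded on January 2021", and reports 517 survivors.
- **WP 1 models.** Under Power Calculation and Statistical Analyses WP 1: "Multilevel models (mixed models) will be used to adjust for the different study sites as random intercepts". Clinical and sociodemographic factors then enter univariable and multivariable models. The reference data are stratified by age and sex.
- **WP 2.** Survivors and controls are compared on physical activity in mixed models, again with site as a random intercept. On older records the plan says: "Whenever the time between participation in WP 1 and recruitment in WP 2 exceeds 3 months, PA will be remeasured by accelerometers". Controls are friends, siblings or contacts of the Swiss study team, and no WP 1 record is described for them.
- **Season.** No month, season or date of wear appears in the accelerometer section, the list of variables, or the WP 1 and WP 2 analysis text.

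**The concern.** One week stands for each child's habitual activity, and that week falls in some season. If activity varies over the year, part of the spread in cpm is calendar rather than child. A site intercept takes up the average level of a site. It does nothing about the difference between winter and summer wearers at the same site.

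The certain consequence of any seasonal effect would be extra residual variance in the models for cpm, sedentary time and the 60-minute recommendation. Bias would need a further condition in one of three places:

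- **Correlates:** month of wear is associated with the factor under study within sites.
- **Survivors against WP 2 controls:** the two groups were measured in different months. A survivor may keep a WP 1 record up to 3 months old at WP 2 recruitment, while a control is measured in WP 2.
- **Survivors against reference data:** the reference studies had a different seasonal mix. Stratifying by age and sex does not address this.

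**Working it through.** The plan gives no figure for season, so there is none to reproduce. The WP 1 sample size is not used here.

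**Inputs from the plan:** reference mean 549 cpm, SD 180 cpm, planned difference 55 cpm (494 against 549), 517 survivors included, and the dates quoted above.

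**Assumption, not in the documents:** a sinusoidal season peaking in mid-June, with amplitude A of 5%, 10% or 15% of 549, that is 27.5, 54.9 or 82.4 cpm, and wear spread evenly over the months of each window.

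**1. Noise.** A sinusoid sampled evenly over the year has variance A²/2. The total variance is 180² = 32,400.

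| Amplitude | A²/2 | Share of 32,400 | Fall in standard error if removed, 1 − √(1 − share) |
|---|---|---|---|
| 5% | 377 | 1.2% | 0.6% |
| 10% | 1,507 | 4.7% | 2.4% |
| 15% | 3,391 | 10.5% | 5.4% |

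This treats the SD of 180 as already containing season. If it did not, the shares would be A²/2 divided by (32,400 + A²/2), or 1.1%, 4.4% and 9.5%. Either way the range is about 1% to 10%.

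**2. Site windows that the dates allow.**

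| Window to January 2021 | Months | In October-January |
|---|---|---|
| Oslo, from November 2016 | 51 | 19 (37%) |
| A site opening July 2018 | 31 | 12 (39%) |
| A site opening October 2020 | 4 | 4 (100%) |

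The mean of the cosine over these windows is −0.054, −0.060 and −0.808.

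- July 2018 site against Oslo: a difference of about −0.007 × A, or 0.2, 0.4 and 0.5 cpm lower.
- October 2020 site against Oslo: a difference of about −0.754 × A, or 21, 41 and 62 cpm lower.

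The large gap arises only for a site that opened at the last date the text permits. If such a site supplied 5% to 15% of the children (a further assumption), the pooled mean would move by 0.05 × 41 to 0.15 × 41, or about 2 to 6 cpm, at 10% amplitude.

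**3. The 3-month allowance in WP 2.** The largest change in a sinusoid over a quarter of a year is 2 sin(45°) × A = 1.41A, or 39, 78 and 116 cpm. That is the worst case for one survivor-control pair. WP 2 ran from January 2019 to December 2020, two full calendar years. With even accrual, the average of a fixed three-month lag over whole years is zero. A group bias therefore needs uneven accrual, which the documents neither show nor exclude.

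**The case against.** The strongest reply is that an article describes covariates by type and leaves the full list to an analysis plan, so a missing wear-month term shows little. That stands in part. The Results section does say that detailed analysis plans for all four work packages are given in the assessments and statistics section, and that section names site as the design adjustment. A fuller list may still exist elsewhere, and nothing in the text is wrong or contradictory on this point.

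Three stronger readings are tempting, and the documents do not support them.

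- **That sites were measured in very different seasons.** Only Oslo's start is dated, and October 2020 is an upper bound for the last site. WP 3 interviewees were to be drawn from WP 1 at Oslo, Bergen and Copenhagen, and patient and parent interviews ended in July 2020. On the stated plan, Bergen and Copenhagen were therefore in WP 1 before October 2020. No four-month site is shown to exist.
- **That season does pass for site, survivor or correlate differences.** Site is a nuisance term here, not a WP 1 aim. No reason is given why diagnosis, treatment or parental education should follow month of wear. The seasonal mix of the reference studies is unknown. The 55 cpm planned difference is survivors against reference, so it is not the yardstick for a gap between two sites.
- **That the models adjust for site and nothing else.** Clinical and sociodemographic factors enter the multivariable models.

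What remains is that a site intercept and these factors do not remove within-site season.

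**Conclusion.** The point holds as a near-costless improvement, not as an error. The stated physical activity models carry no term for when the device was worn, and the site intercept does not supply one. Under an assumed amplitude of 5% to 15% of 549 cpm, season would account for about 1% to 10% of the cpm variance, and removing it would narrow standard errors by about 0.6% to 5.4%. Bias in the correlate models, the WP 2 comparison or the reference comparison is possible but unproven. It depends on an imbalance in wear month that the documents do not report. The analysts can check for it directly from the data they hold.

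**What to change.** - Add month of wear, taken from the device time stamp, alongside site in all WP 1 physical activity models and in the WP 2 survivor-control activity comparison. Use a sine/cosine pair or four seasons.
- Report the season distribution of wear by site, and by group in WP 2.
- As a sensitivity analysis against the reference data, give survivor means standardised for season.
- Repeat the WP 2 activity comparison in those whose accelerometer record was made within WP 2.

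The 3-month remeasurement rule should be left as it is: WP 2 collection ended in December 2020, so changing the rule now could not produce new records.

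The cost is two degrees of freedom for the sine/cosine pair, or three for four seasons, in 517 children, plus one table and two sensitivity analyses. The accelerometer files sit on a central server and are analysed at one site, so wear dates should be recoverable. No new data are needed.
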